### Allocation concealment

After the allocation, the operator who performed allocation will record the operator’s name, baseline date and type of teeth to be treated in the allocation list. The list will not contain the allocated group name in order to conceal the allocation as well as the participant’s name and ID number for personal information protection. Allocation information will be recorded in the electronic medical record system which research staff cannot check without leaving a record of their browsing history.

### Blinding of participants

Participants will be blinded during this study and disclosure of allocation to participants will be performed in the following cases: (1) participant requests to stop or change the allocated intervention, (2) worsening disease or new disease occurs, (3) continuing this study is judged to be inappropriate for the participant or (4) this study is terminated.

### Intervention

After randomized allocation, the participants in the intervention group will be treated with CAREDYNE Shield, and those in the control group will be treated with Nanoseal by the operator who performed allocation. Prior to the application of CAREDYNE Shield or Nanoseal, dental prophylaxis and water rinse will be performed to remove plaque deposits; the areas to be treated will be isolated with cotton rolls and dried with cotton pellets; two equal proportions of solution A and solution B will be mixed with a micro-brush and applied to the dentin surface for 20 s, followed by rinsing with water. Four weeks after the treatment, clinical assessments will be performed by the examiner who enrolled the participant in this study.

During this study, any other dental treatment to DH teeth are prohibited, and all intervention procedures will be recorded by the operator in an electronic chart to improve adherence to intervention protocols. Discontinuing intervention will be performed in the following case: (1) participant requests to stop or change the allocated intervention, (2) worsening disease or new disease occurs or (3) continuing this study is judged to be inappropriate.

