### Randomized allocation

After enrollment, baseline assessments will be performed by the examiner who enrolled the participant in this study. Randomized allocation will then be performed in a 1:1 ratio by the dentist in charge of the patient with opaque, sealed envelopes prepared before participant recruitment and on which “Nanoseal” or “CAREDYNE Shield” is printed. Participants allocated to the intervention group will be treated with CAREDYNE Shield, while those allocated to the control group will be treated with Nanoseal. The information on the desensitizers used in this study is described in Table 4.

**Table 4 Tab4:** Desensitizers used in this study

**Material**	**Manufacturer**	**Composition**
CAREDYNE Shield	GC Dental Industrial Corporation, Tokyo, Japan	Solution A: fluorozinccalciumsilicate glass Solution B: 10–15% phosphoric acid
Nanoseal	Nippon Shika Yakuhin Co., Ltd., Shimonoseki, Japan	Solution A: fluoroaluminocalciumsilicate glass Solution B: 10% phosphoric acid

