## Discussion

Several limitations associated with the present study warrant mention. First, blinding of operators will not be performed; therefore, the risk of bias in this domain may be unavoidable. Second, the data will be collected just after the participant’s training. Thus, VRS which is easier to understand for participants than a visual analog scale (VAS) will be performed; however, VRS is considered to be less sensitive than VAS [18, 19]. Third, it has been recommended that at least three different stimuli, specifically tactile, cold and air stimuli, should be used for clinical assessments of DH because DH may differ among stimuli [2]. However, only air stimuli will be evaluated in the present study because this study is being performed for sample size calculations, which is based on the primary outcome: the reduction of pain intensity in response to air stimuli. Tactile stimuli will be evaluated as a secondary outcome in a future, large-scale study. The GI and PI will be used as secondary outcomes in the present study. If a reduction in either is observed, the effectiveness of CAREDYNE Shield for the reduction of the GI and PI will be investigated in a future clinical study.

Desensitizers like CAREDYNE Shield and Nanoseal that induce chemical occlusion of dentinal tubules are biocompatible and react only with tooth substance; they can, therefore, be casually applied to subgingival areas and proximal surfaces. Furthermore, for several decades, in-vitro studies have investigated the function of zinc and reported that zinc reduced the demineralization of enamel and dentin and inhibited dentin collagen degradation, plaque growth and biofilm formation [20–24]. Thus, CAREDYNE Shield, which releases zinc ions, may be a useful novel desensitizer that acts not only as a desensitizer but also as a root caries inhibitor.

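### As written, the operator learns the arm before prophylaxis, rinse, isolation and drying, although only mixing and application require it

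*Protocol article*

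**What the plan says.** The Randomized allocation section starts with the baseline visit: "After enrollment, baseline assessments will be performed by the examiner who enrolled the participant in this study". It goes on: "Randomized allocation will then be performed in a 1:1 ratio by the dentist in charge of the patient with opaque, sealed envelopes". These are envelopes "on which “Nanoseal” or “CAREDYNE Shield” is printed".

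The Intervention section takes over from there: "After randomized allocation, the participants in the intervention group will be treated with CAREDYNE Shield". In both arms, whoever did the allocating also gives the treatment. The section then describes one preparation for both products: "Prior to the application of CAREDYNE Shield or Nanoseal, dental prophylaxis and water rinse will be performed to remove plaque deposits", after which "the areas to be treated will be isolated with cotton rolls and dried with cotton pellets". Mixing of the two solutions, a 20 s application and a final rinse follow.

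On operator blinding, the Discussion says that "blinding of operators will not be performed; therefore, the risk of bias in this domain may be unavoidable". Participants are to be blinded (Blinding of participants). The examiner who enrols them is described as blinded to the allocation (Informed consent) and makes both the baseline and the 4-week assessments.

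**The concern.** Preparation of the tooth is part of what each participant receives, and here it is delivered after the operator has learned the arm. The text does not fix how long or how thorough the prophylaxis must be, so there is room for it to differ between arms without anyone intending it.

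The step acts on the surface where the outcomes are measured. Its stated purpose is plaque removal, and one secondary outcome is the change in Plaque Index (PI) at that same surface. The other is the change in Gingival Index (GI) close by. Both products are meant to work by occluding tubules at the dentin surface, so uneven cleaning or drying could also bear on the primary air-stimulus score. Randomisation gives no protection, because the preparation comes after it.

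Two later decisions draw on these data. The trial is meant to inform the sample size of a subsequent study, and the Discussion says that a reduction in GI or PI would lead to a future study of the new product's effect on them. A difference produced by preparation would feed into both.

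**Working it through.** No figure in the plan bears on this point, so the check is a trace of the order of steps, asking of each whether it requires the product name.

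| Step, in the order given | Who | Product name needed? | Section |
|---|---|---|---|
| 1. Baseline assessment | Examiner | No | Randomized allocation |
| 2. Allocation by envelope | Dentist in charge | Reveals it | Randomized allocation |
| 3. Prophylaxis and water rinse | Operator (passive voice in the text) | No | Intervention |
| 4. Isolation and drying | Operator (passive voice) | No | Intervention |
| 5. Mixing, application, final rinse | Operator who allocated | Yes, for mixing and application | Intervention |
| 6. Assessment at 4 weeks | Same examiner as step 1 | No | Intervention; Data collection |

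1. *Is the order really stated?* Allocation is placed directly after baseline in the Randomized allocation section, and the Intervention section opens by placing treatment after allocation. Prophylaxis, rinse, isolation and drying appear only inside that description of treatment. No passage puts any preparation before allocation. The quoted prophylaxis sentence, taken alone, fixes only that preparation precedes application. The order relative to the envelope comes from the two sections read together.

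2. *Does the same person do both?* Treatment is given by the operator who allocated. The preparation sentence is passive, but it sits within that operator's treatment, and no one else is named.

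3. *Is knowledge of the arm needed in steps 3 and 4?* No. One description serves both products. The arms first differ when the solutions are mixed.

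4. *Do the existing safeguards cover it?* Blinded participants protect against biased reporting, and a blinded examiner against biased assessment. Neither governs how the tooth is prepared.

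5. *Would moving step 2 to just before step 5 change anything else?* The clinical procedures, the visits, the planned 40 participants and the Fisher's exact test all stay the same. Baseline is still scored before any plaque is removed.

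6. *Can the bias be sized?* No. The documents give no standard deviation for PI, GI or the pain score, and nothing on how preparation varies between operators or how long its effect lasts. Any number would rest wholly on assumption, so none is given.

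**The case against.** Allocating and then delivering the whole intervention is an ordinary sequence, and the article already lists unblinded operators as its first limitation. Nothing in the text is contradictory. No sentence says when the envelope is opened relative to the prophylaxis. The preparation is the same on paper for both arms, and the operator charts every procedure. The fix is also partial, because mixing and application stay unblinded.

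These points are fair and they limit the weight of the finding. They do not remove it: the natural reading still puts the reveal before steps that do not need it, and disclosing a limitation is no reason to leave it wider than necessary.

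Three stronger readings are tempting, and the documents do not support them:

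- A reader might infer that unequal preparation directly shifts the PI and GI results. Both are changes from baseline to 4 weeks, and nothing shows that a difference in plaque left on the treatment day survives 4 weeks of home care.
- A reader might infer that a planned PI or GI comparison would be distorted by some fraction of its standard error. The Statistical design section names a test for the primary outcome only and rules out additional analyses, and there is no input from which to calculate such a fraction.
- A reader might infer that the article declares operator bias unavoidable outright. It says only that the risk may be.

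**Conclusion.** The point holds as a low-severity improvement to the design. The sequence as written exposes four preparation steps (prophylaxis, rinse, isolation, drying) to an operator who knows the arm, without need. What remains is performance bias only, of unknown size and direction. It could reach the air-stimulus score and the PI and GI changes, but the documents do not show that it would. For these preparation steps the Discussion's statement about unavoidable risk does not hold; for mixing and application it may.

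This rests on three assumptions: that allocation precedes preparation, as the two sections read together imply; that the allocating operator also does the preparation; and that the product name cannot be read until the envelope is opened. The wording leaves the last of these open, and the fix depends on it. If practice already differs from the text on the order of steps, the text should be corrected to say so.

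**What to change.** For participants not yet treated, state in the Randomized allocation and Intervention sections that the envelope is taken up and opened only after prophylaxis, rinse, isolation and drying, and immediately before mixing. State also that it is opened out of the participant's sight, because it carries the product name and the participant is in the chair. Keep the baseline assessment where it is, before the prophylaxis, and confirm that the name cannot be read through or on the sealed envelope. In the Discussion, narrow the limitation to operators being unblinded for mixing and application.

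No added staff, visit, procedure or participants are needed, and the analysis does not change. The costs are a short delay at the chairside and a minor amendment while recruitment is under way. Participants treated before the amendment will have been handled under the existing order, so the change date should be recorded and the report should say that two sequences were used.

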### Primary outcome

The primary outcome is the reduction of pain intensity in response to air stimuli measured with a 5-point verbal rating scale (VRS) from baseline to 4 weeks after the intervention. To evaluate the pain level, an air blast will be applied using a three-way dental syringe after the isolation of the DH teeth with cotton rolls, participants will then be asked verbally to rate the level of pain intensity using a 5-point VRS (numerical scale from 0 to 4 summarized in Table 5).

**Table 5 Tab5:** Verbal rating scale

**Score**	**Level of pain intensity**
0	No pain
1	Mild pain
2	Moderate pain
3	Severe pain
4	Extremely intense pain

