### Sample size

No previous clinical studies have investigated the effectiveness of CAREDYNE Shield on DH; therefore, at least 15 participants will be required in each group to perform a sample size calculation in a subsequent study [15]. With a 20% dropout rate, a total of 40 participants will be recruited in this study.

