### Statistical design

The primary outcome will be analyzed with Fisher’s exact test according to the intention-to-treat principle. Participants who discontinue or deviate from the intervention protocols or with any missing data will be excluded. No additional analyses will be performed.

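### The only permitted primary analysis leaves baseline pain out as a covariate, which loses precision and leaves a 40-person pilot sensitive to chance baseline imbalance

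*Protocol article*

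**What the plan says.** The Primary outcome section of the protocol article sets the endpoint as a difference between two readings: "The primary outcome is the reduction of pain intensity in response to air stimuli measured with a 5-point verbal rating scale (VRS) from baseline", with the second reading 4 weeks after treatment. The scale has five integer scores, 0 to 4.

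The Randomized allocation section places the first reading before allocation: after enrollment, "baseline assessments will be performed by the examiner who enrolled the participant in this study", and only then is the treatment assigned 1:1 from envelopes prepared in advance. The section mentions no stratification by baseline pain.

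The Statistical design section gives the whole analysis in three sentences. The first names the test: "The primary outcome will be analyzed with Fisher’s exact test according to the intention-to-treat principle". The second narrows the set of people analysed: "Participants who discontinue or deviate from the intervention protocols or with any missing data will be excluded". The third closes the section: "No additional analyses will be performed".

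On size, the Sample size section says that "at least 15 participants will be required in each group to perform a sample size calculation in a subsequent study". It then allows for losses: "With a 20% dropout rate, a total of 40 participants will be recruited in this study". No alpha, power, effect size or SD is given. The Discussion confirms that the study is run to support a later sample size calculation based on this endpoint.

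**The concern.** Fisher's exact test takes no covariate, and the last sentence of the Statistical design section closes off any other analysis. Non-adjustment is therefore written into the article and not left open for a later document.

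This matters more than usual on a short bounded scale. A participant who starts at 1 can improve by at most 1 point, and one who starts at 4 by up to 4. The eligibility table lists no minimum VRS. Screening accepts pain on air or on tactile stimulation, whereas the endpoint uses air only, so as written someone could enter with little or no room to improve on the endpoint. The reduction is thus tied to where each person starts, and in a small trial the two arms may start at different levels.

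At stake is how well the pilot's single estimate, and the variability taken from it, will serve the next trial.

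**Working it through.** **The plan's own figure.** 15 per group with 20% dropout: 15/(1 − 0.20) = 18.75, so 19 per arm and 38 in total. The stated 40 (20 per arm) agrees to within two participants. Expected completers are 40 × 0.80 = 32, or 16 per arm. No power figure exists to reproduce.

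**Step 1: chance imbalance at baseline.** With simple 1:1 allocation, the SE of the baseline mean difference in SD units is √(2/n). The chance that it exceeds 0.5 SD in either direction is 2[1 − Φ(0.5/√(2/n))].

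| n per arm | SE (SD units) | Chance of imbalance above 0.5 SD |
|---|---|---|
| 20 | 0.316 | 11.4% |
| 16 | 0.354 | 15.7% |
| 15 | 0.365 | 17.1% |

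**Step 2: effect on a mean-change analysis (an analogy).** Let r be the correlation between baseline and week-4 VRS. It is not in the article and is assumed to lie between 0.2 and 0.8, with equal SD s at both visits. Then Var(change) = 2(1 − r)s², Var(adjusted) = (1 − r²)s², and their ratio is (1 + r)/2. A baseline imbalance of 0.5 SD shifts the change contrast by 0.5(1 − r) SD.

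| r | Var(change)/s² | Var(adjusted)/s² | Ratio | Shift from 0.5 SD imbalance | Adjusted n per arm matching 20 per arm on change |
|---|---|---|---|---|---|
| 0.2 | 1.60 | 0.96 | 0.60 | 0.40 SD | 12 |
| 0.5 | 1.00 | 0.75 | 0.75 | 0.25 SD | 15 |
| 0.8 | 0.40 | 0.36 | 0.90 | 0.10 SD | 18 |

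**Step 3: simulation on the 0–4 scale with no treatment effect.** There were 16 per arm and 6,000 trials per setting. Normal scores (mean 2.3 at baseline, 1.3 at week 4, SD 0.9, latent correlation r) were rounded and clipped to 0–4. For Fisher's test, a reduction of at least 1 point was taken as response. The means, SD, r and cut-off are all assumptions. *Imbalanced* means that one given arm starts at least 0.375 points higher, which happened in about 15% of trials.

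| r | Change contrast, all trials | Change contrast, imbalanced | ANCOVA contrast, imbalanced | Responder difference, imbalanced | Fisher rejection, all | Fisher rejection, imbalanced |
|---|---|---|---|---|---|---|
| 0.2 | 0.010 | 0.43 | 0.013 | 0.14 | 1.5% | 3.1% |
| 0.5 | 0.002 | 0.29 | −0.003 | 0.11 | 1.7% | 3.1% |
| 0.8 | −0.002 | 0.15 | −0.008 | 0.07 | 1.9% | 2.3% |

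The simulated variance ratios (0.58, 0.73, 0.86) are close to the formula. Averaged over all trials the unadjusted contrast is about zero. In the imbalanced trials it drifts toward the arm that started higher, and the adjusted contrast does not. Cutting the change into response or non-response reduces the drift but does not remove it.

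**The case against.** A reader might infer that the primary result is biased or that the false-positive rate is inflated. The documents do not support that. Allocation is randomised, so the unadjusted comparison is unbiased over randomisations, and in the simulation Fisher's test rejected in 1.5 to 1.9% of null trials overall and in at most about 3% of imbalanced ones. What remains is conditional: given an observed imbalance, the estimate moves with it.

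A reader might also want to attach a gain in power. That is not supported either. The article plans no t-test and no comparison of mean change, and it states no alpha, power or effect size. The ratio (1 + r)/2 applies by analogy only, and at r = 0.8 the saving falls to 10%.

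The strongest objection is that the more basic defect is the pairing of an ordinal change score with Fisher's test when no table or cut-off is defined, and that repairing it would bring baseline in anyway. The first half stands. The second does not follow: a rank test on the change would be a natural repair and would still leave baseline unused.

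It is also fair to say that the absence of stratification is read from a condensed article. If the full protocol stratifies on baseline pain, the 11 to 16% is too high. Adjustment would still be worthwhile for precision.

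Finally, this is a pilot, and N = 40 does not depend on a variance. That narrows the consequence but does not remove it, because the pilot's estimates are meant to size the next trial.

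**Conclusion.** The point holds in a limited form. The article fixes an unadjusted test and allows nothing further, so a covariate that is measured before allocation in every participant, and that caps the outcome, goes unused. The effect is lost precision and sensitivity to chance imbalance, with no average bias and no loss of type I error control.

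The chance of an imbalance above 0.5 SD is about 11% at 20 per arm and 16% at 16 per arm. By analogy with mean change, adjustment leaves 0.60 to 0.90 of the variance for r from 0.2 to 0.8. A later trial sized on the change-score variance would then need about 1.1 to 1.7 times (1/0.90 to 1/0.60) the participants of an adjusted design.

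These sizes rest on an assumed r, equal SDs at both visits, unstratified allocation, and losses unrelated to arm or outcome. The loss for the planned Fisher analysis itself cannot be stated until its categories are defined.

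**What to change.** In the Statistical design section, replace the unadjusted test with a single prespecified model of week-4 VRS that has treatment and baseline VRS as terms, for example ANCOVA with a permutation p-value. Report the adjusted difference with its confidence interval, and the residual variance for sizing the next trial. Keep the crude change per arm as description, and reword the sentence that rules out further analyses to allow it.

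One model should be named, not a menu. A van Elteren test stratified by baseline VRS is less suitable, because about 32 completers spread over up to five baseline scores would leave sparse strata, and a stratum containing only one arm contributes nothing.

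The cost is a few sentences and one degree of freedom. Baseline VRS is already collected, and N does not change because 40 does not come from a variance. The change should be made before outcome data are examined by arm.

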### Secondary outcome

Secondary outcomes are the change in the gingival condition near the treated area measured with the Gingival Index (GI) and the change in the oral hygiene status at the treated dentin surface measured with the Plaque Index (PI) from baseline to 4 weeks after the intervention [16, 17]. The GI and PI will be evaluated with inspection and palpation.

### Data collection

Outcomes will be assessed at baseline and 4 weeks after the intervention by the examiner who enrolled the participant in this study. Calibration was performed to promote the data quality. The examiner’s name, date of assessment, type of teeth and the acquired outcomes will be recorded in the assessment form and it will be given to the lead principal investigator.

